#### Analysis of proportion

A confidence interval is calculated based on the exact binomial distribution.

#### Analysis of PPV, sensitivity, and specificity

For cases where the histological tumor invasion depth is obtained after endoscopic resection or esophagectomy, the PPV, sensitivity, and specificity will be calculated as described above, and *p*-values will be calculated using Fisher's exact test, if necessary.

The PPV of the standard-depth evaluation is calculated for cMM/SM1 as follows:cMM/SM1$$\mathrm{PPV}(\%)=(\mathrm{number}\;\mathrm{of}\;\mathrm{lesions}\;\mathrm{diagnosed}\;\mathrm{as}\;\mathrm{cMM}/\text{SM}1\;\mathrm{and}\;\mathrm{positive}\;\mathrm{for}\;\mathrm{pMM}/\text{SM}1)/(\mathrm{total}\;\mathrm{number}\;\mathrm{of}\;\mathrm{lesions}\;\mathrm{diagnosed}\;\mathrm{as}\;\mathrm{cMM}/\text{SM}1)\times100=\text{B}/(\text{A}+\text{B}+\text{C})\times100$$

The PPV in the hypothetical-depth evaluation will be calculated for cEP/LPM, cMM/SM1, and cSM2-3 as follows:cEP/LPM$$\mathrm{PPV}\;(\%)=(\mathrm{number}\;\mathrm{of}\;\mathrm{lesions}\;\mathrm{diagnosed}\;\mathrm{as}\;\mathrm{cEP}/\mathrm{LPM}\;\mathrm{and}\;\mathrm{positive}\;\mathrm{for}\;\mathrm{pEP}/\text{LPM})/(\mathrm{total}\;\mathrm{number}\;\mathrm{of}\;\mathrm{lesions}\;\mathrm{diagnosed}\;\mathrm{as}\;\mathrm{cEP}/\text{LPM})\times100=\text{a}/(\text{a}+\text{b}+\text{c})$$cMM/SM1$$\text{PPV}\;(\%)=(\mathrm{number}\;\mathrm{of}\;\mathrm{lesions}\;\mathrm{diagnosed}\;\mathrm{as}\;\mathrm{cMM}/\text{SM}1\;\mathrm{and}\;\mathrm{positive}\;\mathrm{for}\;\mathrm{pMM}/\text{SM}1)/(\mathrm{total}\;\mathrm{number}\;\mathrm{of}\;\mathrm{lesions}\;\mathrm{diagnosed}\;\mathrm{as}\;\mathrm{cMM}/\text{SM}1)\times100=\text{d}/(\text{d}+\text{e}+\text{f}).$$cSM2-3$$\text{PPV}(\%)=(\mathrm{number}\;\mathrm{of}\;\mathrm{lesions}\;\mathrm{diagnosed}\;\mathrm{as}\;\mathrm{cSM}2-3\;\mathrm{and}\;\mathrm{pSM}2-3)/(\mathrm{total}\;\mathrm{number}\;\mathrm{of}\;\mathrm{lesions}\;\mathrm{diagnosed}\;\mathrm{as}\;\mathrm{cSM}2-3)\times100=\text{i}/(\text{g}+\text{h}+\text{i})$$

The sensitivity and specificity of cEP/LPM, cMM/SM1, and cSM2-3 will be calculated for depth evaluation as follows:cEP/LPM$$\mathrm{Sensitivity}\;(\%)=(\mathrm{number}\;\mathrm{of}\;\mathrm{lesions}\;\mathrm{diagnosed}\;\mathrm{as}\;\mathrm{cEP}/\mathrm{LPM}\;\mathrm{and}\;\mathrm{confirmed}\;\mathrm{as}\;\mathrm{pEP}/\text{LPM})/(\mathrm{number}\;\mathrm{of}\;\mathrm{lesions}\;\mathrm{confirmed}\;\mathrm{as}\;\mathrm{pEP}/\text{LPM})\times100=\text{a}/(\text{a}+\text{d}+\text{g})\times100$$$$\text{Specificity}(\%)=(\mathrm{number}\;\mathrm{of}\;\mathrm{lesions}\;\mathrm{not}\;\mathrm{diagnosed}\;\mathrm{as}\;\mathrm{cEP}/\mathrm{LPM}\;\mathrm{and}\;\mathrm{confirmed}\;\mathrm{as}\;\mathrm{pEP}/\text{LPM})/(\mathrm{number}\;\mathrm{of}\;\mathrm{lesions}\;\mathrm{not}\;\mathrm{confirmed}\;\mathrm{as}\;\mathrm{pEP}/\text{LPM})\times100=(\text{e}+\text{h}+\text{f}+\text{i})/(\text{b}+\text{e}+\text{h}+\text{c}+\text{f}+\text{i})\times100$$cMM/SM1$$\mathrm{Sensitivity}(\%)=(\mathrm{number}\;\mathrm{of}\;\mathrm{lesions}\;\mathrm{diagnosed}\;\mathrm{as}\;\mathrm{cMM}/\text{SM }1\;\mathrm{and}\;\mathrm{confirmed}\;\mathrm{as}\;\mathrm{pMM}/\text{SM}1)/(\mathrm{number}\;\mathrm{of}\;\mathrm{lesions}\;\mathrm{confirmed}\;\mathrm{as}\;\mathrm{pMM}/\text{SM}1)\times100=\text{e}/(\text{b}+\text{e}+\text{h})\times100$$$$\text{Specificity }(\%)=(\mathrm{number}\;\mathrm{of}\;\mathrm{lesions}\;\mathrm{not}\;\mathrm{diagnosed}\;\mathrm{as}\;\mathrm{cMM}/\text{SM}1\;\mathrm{and}\;\mathrm{confirmed}\;\mathrm{as}\;\mathrm{pMM}/\text{SM}1)/(\mathrm{number}\;\mathrm{of}\;\mathrm{lesions}\;\mathrm{not}\;\mathrm{confirmed}\;\mathrm{as}\;\mathrm{pMM}/\text{SM}1)\times100=(\text{a}+\text{g}+\text{c}+\text{i})/(\text{a}+\text{d}+\text{g}+\text{c}+\text{f}+\text{i})\times100$$cSM2-3$$\text{Sensitivity}(\%)=(\mathrm{number}\;\mathrm{of}\;\mathrm{lesions}\;\mathrm{diagnosed}\;\mathrm{as}\;\mathrm{cSM}2-3\;\mathrm{and}\;\mathrm{confirmed}\;\mathrm{as}\;\mathrm{pSM}2-3)/(\mathrm{number}\;\mathrm{of}\;\mathrm{lesions}\;\mathrm{confirmed}\;\mathrm{as}\;\mathrm{pSM}2-3)\times100=\text{i}/(\text{c}+\text{f}+\text{i})\times100$$$$\text{Specificity }(\%)=(\mathrm{number}\;\mathrm{of}\;\mathrm{lesions}\;\mathrm{not}\;\mathrm{diagnosed}\;\mathrm{as}\;\mathrm{cSM}2-3\;\mathrm{and}\;\mathrm{confirmed}\;\mathrm{as}\;\mathrm{pSM}2-3)/(\mathrm{number}\;\mathrm{of}\;\mathrm{lesions}\;\mathrm{not}\;\mathrm{confirmed}\;\mathrm{as}\;\mathrm{pSM}2-3)\times100=(\text{a}+\text{d}+\text{b}+\text{e})/(\text{a}+\text{d}+\text{g}+\text{b}+\text{e}+\text{h})\times100$$

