#### Analysis of the primary endpoint

The calculation formula for the standard-depth evaluation is: (lesions diagnosed as cMM/SM1 and pMM/SM1 [B]) / (total lesions [A + B + C]) (Table 3), and for the depth evaluation, [(lesions diagnosed as cEP/LPM and pEP/LPM [a]) + ((lesions diagnosed as cMM/SM1 and pMM/SM1 [e]) + (lesions diagnosed as cSM2-3 and pSM2-3 [i]))] / (total lesions [a + b + c + d + e + f + g + h + i]) (Table 4). A point estimate is calculated for accuracy, and a 95% confidence interval is calculated based on the exact binomial distribution. The corresponding *p*-value is also calculated.

**Table 3 Tab3:** Relationship between standard depth evaluation and histological depth diagnosis

	pEP/LPM	pMM/SM1	pSM2-3
cMM/SM1 (B2 vessel)	A	B	C

$$\begin{array}{l}\mathrm{Accuracy}\;\mathrm{of}\;\mathrm{standard}-\mathrm{depth}\;\mathrm{evaluation}\;(\%)\\=(\mathrm{number}\;\mathrm{of}\;\mathrm{lesions}\;\;\mathrm{diagnosed}\;\mathrm{as}\;\mathrm{cMM}/\text{SM}1\;\mathrm{and}\;\mathrm{confirmed}\;\mathrm{as}\;\mathrm{pMM}/\text{SM}1)/(\mathrm{total}\;\mathrm{number}\;\mathrm{of}\;\mathrm{lesions})\times100=\lbrack\text{B}\rbrack/\lbrack\text{A}+\text{B}+\text{C}\rbrack\text{x}100\end{array}$$

*MM* Muscularis mucosa, *SM1* Upper third of the submucosal layer, *EP/LPM* Epithelial/lamina propria

**Table 4 Tab4:** Relationship between hypothetical depth evaluation and histological depth diagnosis

	pEP/LPM	pMM/SM1	pSM2-3
cEP/LPM (B2 vessel area ≤ 4 mm)	a	b	c
cMM/SM1 (B2 vessel area between 4–10 mm without additional findings^a^)	d	e	f
cSM2-3 (B2 vessel area ≥ 10 mm or macroscopic type 0-I/0-III in B2 vessel area)	g	h	i

^a^Additional findings: B2 vessel area ≤ 4 mm, B2 vessel area ≥ 10 mm, macroscopic type 0-I/0-III in B2 vessel area

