
#### Analysis of likelihood ratios

For cases in which the histological tumor invasion depth is obtained after endoscopic resection or esophagectomy, the likelihood ratios will be calculated as sensitivity / (1-specificity) for each additional finding, such as B2 vessel area ≤ 4 mm, B2 vessel area ≥ 10 mm, and macroscopic type 0-I/0-III in the B2 vessel area.

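### The three specificity numerators are wrong in words and the cMM/SM1 PPV is wrong in letters, so neither reading alone gives a correct set of secondary endpoints

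*Protocol article*

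**What the plan says.** Table 4 (Protocol article, Analysis of the primary endpoint) cross-tabulates the hypothetical-depth diagnosis against pathology. The columns are pEP/LPM, pMM/SM1 and pSM2-3. The rows are:

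- a, b, c: "cEP/LPM (B2 vessel area ≤ 4 mm")
- d, e, f: "cMM/SM1 (B2 vessel area between 4–10 mm without additional findings")
- g, h, i: "cSM2-3 (B2 vessel area ≥ 10 mm or macroscopic type 0-I/0-III in B2 vessel area")

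Under Analysis of PPV, sensitivity, and specificity, the article announces: "The sensitivity and specificity of cEP/LPM, cMM/SM1, and cSM2-3 will be calculated for depth evaluation as follows". Each formula is then written twice in one equation, first in words and then in Table 4 letters. For the EP/LPM specificity, the equation source for the worded numerator reads "not}\;\mathrm{diagnosed}\;\mathrm{as}\;\mathrm{cEP}/\mathrm{LPM}\;\mathrm{and}\;\mathrm{confirmed}\;\mathrm{as}\;\mathrm{pEP}/\text{LPM", and the letters after the equals sign read "e}+\text{h}+\text{f}+\text{i})/(\text{b}+\text{e}+\text{h}+\text{c}+\text{f}+\text{i})\times100". The MM/SM1 and SM2-3 specificities follow the same pattern.

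In the same section, the hypothetical-depth PPV for cMM/SM1 is worded as cMM/SM1 lesions that are pMM/SM1 over all cMM/SM1 lesions, but is lettered d/(d+e+f).

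Two other places use these quantities. Under Analysis of likelihood ratios, "the likelihood ratios will be calculated as sensitivity / (1-specificity) for each additional finding", with no cell formula of its own. The Discussion says the results will be interpreted after confirming that the cMM/SM1 PPV is higher under the hypothetical-depth evaluation than under the standard one.

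**The concern.** PPV, sensitivity, specificity and likelihood ratio are all named secondary endpoints, and this section is where the article fixes how they are computed. In four of its equations the two sides of the equals sign are different quantities. The faults also run in opposite directions: for specificity the letters are right and the words wrong, while for the cMM/SM1 PPV the words are right and the letters wrong. A rule such as *use the cell formulas* or *use the verbal definitions* therefore cannot rescue the section. It has to be repaired equation by equation.

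The PPV slip has the more direct consequence. The article names the cMM/SM1 PPV comparison as a check to be made before the results are interpreted. A PPV computed from the printed letters could make a favourable result look like a failure of that check.

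**Working it through.** **Step 1: the plan's own figures.** The article gives no numerical specificity or PPV target to reproduce here. Its lesion count serves only as the size of the example. Exact one-sample binomial, 50% against 65%, two-sided 0.05: at n = 121 the rule is at least 72 correct, with upper-tail probability 0.0225 and power 0.912. Inflating for 10% dropout, 121/0.9 = 134.4, rounded up to 135. Both stated figures reproduce, and nothing below depends on them.

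**Step 2: map words and letters to Table 4.** Specificity for class X is true negatives over all lesions that are not pX.

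| Class | Numerator as worded | Numerator as lettered | Denominator (words and letters agree) |
|---|---|---|---|
| EP/LPM | d+g | e+h+f+i | b+e+h+c+f+i |
| MM/SM1 | b+h | a+g+c+i | a+d+g+c+f+i |
| SM2-3 | c+f | a+d+b+e | a+d+g+b+e+h |

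The lettered numerators are the true negatives in all three rows. The worded numerators are the false negatives, and none of their cells appears in the denominator, so the worded quantity is not a proportion. For a perfect test it would be 0%.

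**Step 3: the cMM/SM1 PPV.** Cell d holds cMM/SM1 lesions that proved pEP/LPM, and cell e holds those that proved pMM/SM1. The words give e/(d+e+f). The letters give d/(d+e+f), which is the share of cMM/SM1 calls that were too deep.

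**Step 4: size on an assumed table.** Assumption: 121 lesions split 33/67/21 by pathology, close to the 27.4/55.7/17.0% quoted in the Background, with 79 correct (65.3%). Rows: 17, 12, 2; 13, 48, 5; 3, 7, 14.

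- Specificity by cells: 74/88 = 84.1%, 36/54 = 66.7%, 90/100 = 90.0%.
- Specificity by words: 16/88 = 18.2%, 19/54 = 35.2%, 7/100 = 7.0%.
- Sensitivity: 17/33 = 51.5%, 48/67 = 71.6%, 14/21 = 66.7%.
- Sensitivity/(1 − specificity), per depth class: 3.24, 2.15, 6.67 by cells; 0.63, 1.11, 0.72 by words.
- cMM/SM1 PPV: 48/66 = 72.7% by words, 13/66 = 19.7% by letters. Standard-depth PPV: 67/121 = 55.4%.

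**Step 5: range over other assumed tables** (same pathology split).

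| Rows (a,b,c / d,e,f / g,h,i) | Correct | Specificity by cells, % | Specificity by words, % | PPV e/(d+e+f) | PPV d/(d+e+f) |
|---|---|---|---|---|---|
| 13,17,4 / 13,34,7 / 7,16,10 | 57/121 = 47.1% | 76.1 / 63.0 / 77.0 | 22.7 / 61.1 / 11.0 | 34/54 = 63.0% | 13/54 = 24.1% |
| 21,13,1 / 9,44,6 / 3,10,14 | 79/121 = 65.3% | 84.1 / 72.2 / 87.0 | 13.6 / 42.6 / 7.0 | 44/59 = 74.6% | 9/59 = 15.3% |
| 30,3,0 / 2,60,2 / 1,4,19 | 109/121 = 90.1% | 96.6 / 92.6 / 95.0 | 3.4 / 13.0 / 2.0 | 60/64 = 93.8% | 2/64 = 3.1% |

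From the worst table to the best, the worded specificity falls as the test improves. In every table the correct PPV lies above 55.4% and the lettered one below it.

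**The case against.** The strongest reply is that the right answer is already on the page. All three specificity cell formulas are correct, as are the worded denominators, and the defect is one dropped *not* per numerator. The *not* may have been meant to govern both clauses. A trained analyst would probably notice a numerator that lies outside its denominator, and would probably also notice that the accuracy and sensitivity formulas use e and not d for correct cMM/SM1 calls. A separate analysis plan may hold correct formulas. No success criterion rests on specificity.

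Much of this stands, and it limits the point to a correction. It does not remove it. The text nowhere says that *not* covers both clauses, and the denominator repeats its own *not*. The rule that rescues specificity, trusting the cells, is the one that breaks the PPV. These are explicit statements that contradict each other, not details left to another document.

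A reader might go further and infer that the likelihood ratios will be wrong, or that informative findings would seem to point the wrong way. The documents do not support that:

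- The likelihood-ratio section gives only the ratio and does not refer to the faulty wording, so an analyst could equally work from the correct letters.
- Its ratios are per finding (≤ 4 mm, ≥ 10 mm, 0-I/0-III), whereas the ratios in the working are per depth class.
- MM/SM1 is not an additional finding, and the cSM2-3 row pools two findings.
- A lesion of ≤ 4 mm with 0-I/0-III is classed as cSM2-3, so even the cEP/LPM row is not the same as the ≤ 4 mm finding.

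**Conclusion.** The point holds as an internal contradiction in four stated formulas for named secondary endpoints: three specificity numerators wrong in words, and one PPV numerator wrong in letters. The mapping to Table 4 is exact and needs no assumption.

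The sizes are illustrative, because every 3×3 table used is assumed. They show that the two readings are far apart, not what the trial will report. The PPV letter error matters most, because it can reverse the comparison with standard evaluation that the Discussion says will be confirmed before interpretation.

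An analysis programmed from the specificity cells and the PPV words would be correct throughout. The primary endpoint, its accuracy formulas and the sample size are untouched. Nothing is shown about the direction of any likelihood ratio for an individual finding.

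**What to change.** 1. In each of the three specificity equations, reword the numerator to *number of lesions not diagnosed as cX and not confirmed as pX*, and keep the cell formulas as they are.
2. Change the letters of the hypothetical-depth cMM/SM1 PPV to e/(d+e+f), and keep the words.
3. Add one sentence under Analysis of likelihood ratios: for each additional finding, specificity is true negatives over all lesions without the corresponding pathological depth, as in the corrected formulas.

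The cost is three wording corrections, one letter and one sentence. Data collection, sample size and the primary analysis do not change.

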
#### Analysis of likelihood ratios

For cases in which the histological tumor invasion depth is obtained after endoscopic resection or esophagectomy, the likelihood ratios will be calculated as sensitivity / (1-specificity) for each additional finding, such as B2 vessel area ≤ 4 mm, B2 vessel area ≥ 10 mm, and macroscopic type 0-I/0-III in the B2 vessel area.

#### Relation between size of B2 vessel area and histological tumor invasion depth

For cases in which the histological tumor invasion depth is obtained after endoscopic resection or esophagectomy, a paired-samples t-test will be performed to reject the null hypothesis test, which is whether the two groups of pEP/LPM and pMM/SM1 are equal in size of the observed B2 vessel area. The pMM/SM1 and pSM2-3 groups will use the same test. The cut-off value will be calculated based on the receiver operating characteristic (ROC) curve.

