## Methods

### Study design

This is a multicenter prospective observational study. Endoscopic examinations will be performed in 13 hospitals in Japan. Tumor invasion depth will be evaluated based on only the JES classification (standard-depth evaluation) and the JES classification with additional findings (hypothetical-depth evaluation) for the same patients (Fig. 1). The study protocol will be performed following the Declaration of Helsinki and is approved by the Ethical Review Board of Shizuoka Cancer Center (IRB approval number: T2022–53–2022-1–2). The trial is registered in the Clinical Trials Registry of the University Hospital Medical Information Network (UMIN-CTR) as UMIN000051145. The date of the first registration was 23/5/2023.

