#### Hypothetical depth evaluation

Before initiating the study, we verified the sizes of biopsy forceps available in the market and gained an understanding of the forceps sizes used at each facility. Based on this information, the area of the type B2 vessel will be measured in millimeters using the forceps size as a guide. Measurements < 1 mm will be rounded to 1 mm. If Type B2 vessels are present in multiple areas, then the largest area will be recorded. Macroscopic types are defined following the Treatment Guidelines for Esophageal Cancer [14, 15]. Namely, 0-I is defined as a protruding lesion that is ≥ 1 mm in height, and 0-III is a depressed lesion that is estimated to reach the muscularis mucosa or deeper.

The criteria for judging tumor invasion depth are discussed multiple times by the JES superficial esophageal cancer depth diagnosis criteria study group, and a consensus is reached (Table 2). The anticipated high diagnostic concordance using biopsy forceps as a reference led to the omission of central evaluation in this study.A Lesion with a Type B2 vessel area of ≤ 4 mm is diagnosed as cEP/LPM.A lesion with a Type B2 vessel area of ≥ 10 mm is diagnosed as cSM2-3.I and/or 0-III macroscopic types of the Type B2 vessel area are diagnosed as cSM2-3.When conflicting findings of a B2 vessel area of ≤ 4 mm and 0-I/0-III or Type B2 vessel area are observed in one Type B2 vessel area, the lesion is diagnosed as cSM2-3.When multiple Type B2 vessel areas are observed, the depth is determined based on the deepest finding. Specifically, the order of adoption is 0-I/0-III of Type B2 vessel area, the size of B2 vessel area ≥ 10 mm, the size of Type B2 vessel area between 4 and 10 mm, and the size of Type B2 vessel area ≤ 4 mm.

**Table 2 Tab2:** Criteria for hypothetical depth diagnosis

	Corresponding tumor invasion depth
B2 vessel area ≤ 4 mm	EP, LPM
B2 vessel area between 4–10 mm without additional findings^a^	MM, SM1
B2 vessel area ≥ 10 mm or macroscopic type 0-I/0-III in B2 vessel area	SM2-3

*MM* Muscularis mucosa, *SM1* Upper third of the submucosal layer, *EP/LPM* Epithelial/lamina propria

^a^Additional findings are B2 vessel area ≤ 4 mm, B2 vessel area ≥ 10 mm, and macroscopic type 0-I/0-III in B2 vessel area

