### Histological evaluation

After endoscopic resection, the specimens will be dissected at 2–3 mm intervals, and the histological tumor invasion depth will be determined. In surgical cases, the specimens will be dissected at intervals of 3 mm whenever possible. Histological diagnoses will be made based on the Treatment Guidelines for Esophageal Cancer [14, 15]. The tumor invasion depth is defined as follows: pEP, cancer remains within the epithelium; pLPM, cancer remains within the lamina propria; pMM, cancer invades the muscularis mucosa; pSM1, cancer remains within 200 μm of the submucosa from the muscularis mucosa; and pSM2, cancer invades beyond 200 μm into the submucosa. Desmin immunostaining is recommended for evaluating the muscularis mucosae.

Esophageal squamous cell carcinoma is a disease encountered daily and is not difficult to diagnose. The handling of specimens is also described in detail in the esophageal cancer handling guidelines; therefore, it is assumed that there is a slight variation in diagnosis between facilities. Therefore, in this study, pathological diagnosis is used to determine the histological depth of esophageal cancer, and no central judgment is performed.

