#### Secondary endpoints

The secondary endpoints include the following: the proportion of pSM2-3 when the area in which B2 vessels are observed is > 10 mm, the proportion of pSM2-3 when the macroscopic type of the observed B2 vessel area is 0-I or 0-III, the proportion of pSM2-3 when the area in which B2 vessels are observed is > 10 mm or the macroscopic type is 0-I or 0-III, the proportion of pEP/LPM when the area in which B2 vessels are observed is < 4 mm, PPV, sensitivity, specificity, likelihood ratio, a relation between the size of the B2 vessel area and the histological tumor invasion depth, a relation between the number of B2 vessel areas and the histological tumor invasion depth, and the relationship between the macroscopic type of the B2 vessel area and histological tumor invasion.

Furthermore, if the proportion of pSM2-3 when the area in which B2 vessels are observed is > 10 mm, the proportion of pSM2-3 when the macroscopic type of the observed B2 vessel area is 0-I or 0-III, and the proportion of pEP/LPM when the area in which B2 vessels are observed is < 4 mm exceeds 50%, these findings are considered to have an impact on the clinical diagnosis and are therefore included as secondary endpoints.

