#### Relation between the number of observed B2 blood vessel areas and histological depth

For lesions in which a histological depth diagnosis is obtained through endoscopic resection or esophagectomy, we will also examine the number of observed B2 blood vessel areas (single location vs. multiple locations) between the two groups: pEP/LPM and pMM/SM1 and pMM/SM1 and pSM2-3. Fisher's exact test using p-values for contingency tables will be used for intergroup comparisons.

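### B2 vessel area size is compared between separate histological groups with a paired-samples t-test, although no pairs exist; an independent two-sample test is needed

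*Protocol article*

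**What the plan says.** The Secondary endpoints section lists "a relation between the size of the B2 vessel area and the histological tumor invasion depth". The section on that relation gives the method: "a paired-samples t-test will be performed to reject the null hypothesis test, which is whether the two groups of pEP/LPM and pMM/SM1 are equal" in the size of the observed area. It then adds: "The pMM/SM1 and pSM2-3 groups will use the same test". A cut-off is to be derived separately from an ROC curve.

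Three other places show what kind of data these are:

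- Histological evaluation defines depth as a set of exclusive categories, for example "pSM1, cancer remains within 200 μm of the submucosa from the muscularis mucosa; and pSM2, cancer invades beyond 200 μm into the submucosa".
- Hypothetical depth evaluation fixes the size recorded for a lesion: "If Type B2 vessels are present in multiple areas, then the largest area will be recorded".
- The section on the number of B2 areas compares the same two pairs of histological groups and states: "Fisher's exact test using p-values for contingency tables will be used for intergroup comparisons".

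**The concern.** A paired t-test analyses differences within units that were measured twice, or within deliberately matched pairs. The groups here are formed by the pathology result, so a lesion belongs to exactly one of them. There is no second measurement to subtract.

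At stake is the one hypothesis test pre-specified for the size-depth relation. An analyst following the text must either depart from it or invent pairs. Departing after the data are known weakens the pre-specification. Inventing pairs wastes data and makes the result depend on an arbitrary choice.

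**Working it through.** **1. Are there pairs anywhere in the design?**

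- Histological groups: one depth per lesion, so pEP/LPM, pMM/SM1 and pSM2-3 do not overlap. Tables 3 and 4 use them as separate columns.
- Several B2 areas in one lesion: only the largest counts as the lesion's size. Areas within one lesion also share its single histological depth, so they could not form a pair across groups.
- Matching of lesions across groups: none is described.
- The pairing that does exist, in Study design, is of two evaluations: the standard one and "the JES classification with additional findings (hypothetical-depth evaluation) for the same patients". That is a different comparison from size by depth.
- Fisher's exact test, chosen for the same groups in the next section, treats them as independent.

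**2. Could the group sizes be equal, so that the test would at least run?**

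Standard accuracy is B/(A + B + C), where A, B and C are the numbers of pEP/LPM, pMM/SM1 and pSM2-3 lesions. Equal sizes in both comparisons require A = B = C, which means a standard accuracy of 1/3. The Sample size calculation assumes 50%. At B = 50%, A and C share the other 50%, so one of them can equal B only if the other is empty. On the plan's own assumption, therefore, at least one of the two comparisons has unequal groups. Equal sizes would still not create pairs.

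**3. Illustrative group sizes**

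The article gives no sample size for this test. Its 121 and 135 are for the primary endpoint, and both reproduce. An exact binomial test of 50% against 65% at 0.025 per tail with 121 lesions rejects at 72 or more correct, with upper-tail probability 0.0225 and power 91.2%. For dropout, 121/0.9 = 134.4, rounded up to 135. Neither figure depends on the t-test.

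The Background quotes a retrospective split of 27.4%, 55.7% and 17.0%. Assuming that it carries over to 121 lesions:

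| Group | Calculation | Lesions |
|---|---|---|
| pEP/LPM | 121 × 0.274 = 33.2 | 33 |
| pMM/SM1 | 121 × 0.557 = 67.4 | 67 |
| pSM2-3 | 121 × 0.170 = 20.6 | 21 |

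Forced one-to-one pairing leaves out 67 − 33 = 34 pMM/SM1 lesions in the first comparison and 67 − 21 = 46 in the second. Run on simulated groups of 33 and 67, the paired test stopped with an error because the lengths differ; Welch's test ran.

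**4. What arbitrary pairing would cost**

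With independent values of common variance σ², the mean difference has variance 2σ²/m for m arbitrary pairs, against σ²(1/n₁ + 1/n₂) when all lesions are used.

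- 33 v 67: 2/33 = 0.0606 against 1/33 + 1/67 = 0.0452, a ratio of 1.34.
- 67 v 21: 2/21 = 0.0952 against 1/67 + 1/21 = 0.0625, a ratio of 1.52.

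A simulation with 20,000 replicates, normal data and an assumed true difference of 0.5 SD agrees with this direction:

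| Comparison | Arbitrary pairs: power | Welch: power |
|---|---|---|
| 33 v 67 | 50% | 63% |
| 67 v 21 | 34% | 49% |

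With no true difference, both methods rejected in about 5% of replicates.

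In one simulated data set (33 v 67), 5,000 random choices of which lesions to keep and how to pair them gave paired p-values from 0.00003 to 0.71. Welch's test on the same data gave a single value, 0.020.

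**The case against.** The strongest reply is that this is a wording slip. The authors use Fisher's exact test for the same groups, so they evidently regard them as independent. They propose no pairing, and software would refuse the test on groups of unequal length, so the error would surface at once. No decision rule cites this p-value: the study conclusion rests on accuracy, the 50% thresholds rest on proportions with exact intervals, and the Discussion adds a check on PPV.

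Most of this stands, and it limits the weight of the point. It does not remove it. The text names a specific test, the test is the wrong one, and nothing elsewhere in the article corrects it. Nor is this a detail left to an analysis plan: a plan naming the right test would contradict the published protocol.

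A reader might infer more than the article supports:

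- **That the 4 mm and 10 mm criteria rest on this test.** They come from earlier retrospective studies and study-group consensus. Any new cut-off would come from the ROC curve.
- **That the endpoint is left without any analysis.** Only the t-test fails. The ROC curve, the proportions by size threshold and the likelihood ratios still address size against depth.
- **That false-positive risk is inflated.** The simulation shows about 5% under random pairing. The harm is lost data and an arbitrary result.
- **That the primary comparison has the mirror-image fault.** That is a separate question, which this passage does not settle; the article names exact binomial methods there, not an unpaired two-sample test.
- **That the sizes are known to be skewed.** The article says only that sizes are in millimetres and that values below 1 mm "will be rounded to 1 mm".

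**Conclusion.** The paired-samples t-test is wrong for both size comparisons as written. This follows from the structure of the data alone: one depth and one size per lesion, with no matching. It needs no numerical assumption.

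The sizes given are illustrative. Groups of 33, 67 and 21 assume that a literature split from the Background applies; it is not the plan's own assumption, which is 50% pMM/SM1, or about 60 of 121, with no stated split of the rest. The power figures also assume normal data and a 0.5 SD difference.

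The scope is one test for one secondary endpoint. The study's main conclusion does not depend on it. It should be corrected because the text is plainly wrong and the repair is trivial, not because the trial's result is at risk.

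**What to change.** In the section on B2 vessel area size and histological depth, replace the paired test with an independent two-sample test for both comparisons: pEP/LPM against pMM/SM1, and pMM/SM1 against pSM2-3. Welch's t-test is enough. The Wilcoxon rank-sum test is a reasonable alternative if the sizes prove skewed, and the rule for choosing between them should be written down before the data are examined. Report the estimated difference with a 95% confidence interval alongside each p-value.

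The cost is one sentence. No data collection, sample size or other analysis changes. Any separate analysis plan should carry the same wording.
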